### Study design and setting

2.1

The study is designed as a Phase II clinical trial and is following a randomized, double blinded, placebo controlled, parallel design to examine the efficacy of SOCG in MDD treatment.

Participants will be selected from volunteers based on demographic information, medical history, vital signs, lab examinations, and selection criteria. Selected participants will be assigned to 3 experimental groups and 1 placebo group according to the stratified block randomization. The experimental groups will be a low dose group, a medium dose group, and a high dose group. Participants will be given SOCG or placebo 3 times/day, for 8weeks (56 days). They will be examined using the Korean Version of the Hamilton Depression Rating Scale (K-HDRS), the Korean version of the Beck Depression Inventory-II (K-BDI-II), Korean Symptom Check List-95 (KSCL-95), State Trait Anxiety Inventory-Korean version (STAI-K), State Trait Anger Expression Inventory Korean version (STAXI-K), Insomnia Severity Index (ISI), Instrument on Pattern Identifications for Depression, EuroQol-5 Dimension (EQ-5D), and melatonin and cortisol levels to assess score variation, improvements in quality of life, and biological indicators.

The research progress is summarized in Figure 1 and the examination details followed by visit schedules are shown in Table 1. Each visit should occur at the scheduled date or within ±4 days. The screening tests will be completed 10 days before the second visit (0 week). The results will be examined at the second visit. The lab tests will include hematologic tests for levels of hemoglobin, hematocrit, red blood cell count, white blood cell count, platelet count, and erythrocyte sedimentation rate, and hematochemical tests for levels of aspartate aminotransferase (AST), alanine aminotransferase (ALT), gamma-glutamic transpeptidase (γ-GTP), alkaline phosphatase (ALP), blood urea nitrogen (BUN), creatinine, total bilirubin, glucose, Na+, K+, Cl-, lactate dehydrogenase (LDH), creatine phosphokinase (CPK), and urine tests including dip-stick test and urine microscopy. Urinary human chorionic gonadotropin (hCG) level will be checked 14 days before the second visit for every participant with the possibility of pregnancy, experiencing lack of menstruation for less than 1 year since the last menstrual period.

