#### Safety evaluation

2.5.3

Every participant given the medication at least once will be assessed for occurrence of adverse events and their association with the medication. Potential adverse events include all medical symptoms that will occur during the trial. Every unintended phenomenon, side effects, abnormalities in vital signs, and lab tests will be documented in an adverse events report. The investigator responsible will assess the adverse events at different stages based on their seriousness. The adverse events will be documented to be communicated to the participants and/or their legal representatives immediately and will be notified to the IRBs.

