#### Statistical analysis

2.7.2

The efficacy will be evaluated based on intention-to-treat (ITT) analysis and per-protocol (PP) analysis. Participants with total drug compliance <75% will be excluded from PP analysis.

Continuous data will be represented by mean, standard deviation, minimum, and maximum and categorical data will be represented by a frequency table. We will compare data using analysis of variance (ANOVA) for the continuous variables, and Pearson chi-squared test or Fisher's exact test for the categorical variables. The size of the type I error caused due to multiple comparisons will be modified using Bonferroni's method.

The primary outcome, the changes in the K-HRDS, will be evaluated using analysis of covariance (ANCOVA) with the experimental group, baseline K-HDRS, and the institution as the explanatory variables. The estimates of mean differences between placebo and each SOCG group, the 95% confidence interval, and the *P*-value will be presented. For evaluating the sensitivity of missing values of K-HDRS, the primary outcome observed at each point will be analyzed using the linear mixed model. The explanatory variables include all groups, baseline K-HDRS, institutions, the observation time point, and the interaction term of the experimental group based on the observation time point.

Among the secondary outcomes, recovery rate and remission rate of K-HDRS will be analyzed using logistic regression analysis with the experimental group, baseline K-HDRS, and the institution as the explanatory variables. Estimates of odds ratio of each SOCG group, 95% confidence interval, and *P*-value will be presented using the placebo group as the standard category. The other secondary outcomes will be analyzed using ANCOVA with the experimental group, baseline outcomes, and the institution as the explanatory variables.

For safety assessment, outcomes of lab tests will be compared to the baseline values. Each adverse event will be listed with a detailed explanation, and the frequency will be recorded separately based on correlation with the medication. Adverse events will be summarized based on groups and organs. The ANOVA or Kruskal-Wallis test will be used to compare the frequency of medication-correlated adverse events between groups. The Pearson chi-squared test or Fisher's exact test will be used to compare the percentage of participants who experienced the adverse events at least once between the groups.

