Cortisol is a reliable biomarker that most accurately represents the altered biochemical state in response to stress stimuli.^[54]^ Carroll et al^[55]^ reported that cortisol levels in patients with MDD were two times higher than those in normal subjects. Cortisol also has a circadian rhythm, which is highest in the early morning and lowest in the evening between 8 PM and 2 in adults.^[56]^ Cortisol can also be measured in saliva.

Saliva will be collected using the Salivettes system (Sarstedt, Germany) and the amount of melatonin and cortisol secretion will be measured. Saliva will be collected in a precise manner and stored frozen (−20°C) immediately without contamination. The subject will visit the trial center at a specific time (10 AM ± 1 hour) during visit 1 and visit 6. We will examine the differences in the levels of these 2 hormones in the subjects in comparison to normal values.

Results of preclinical examinations performed in rats thus far have shown the presence of colored stool, dilute stool, mucous stool, diarrhea, and salivation, but no toxicologically significant effects were observed due to SOCG administration. SOCG has not been tested on healthy individuals or patients, and therefore no side effects have been clearly revealed. However, the possibility of some side effects remains, including dyspepsia, diarrhea, dizziness, rash, fatigue, which are usually found to be occurred due to herbal medicines. The chief investigator and the investigator responsible will pay detailed attention to the safety of the participants and minimize any potential damage by carrying out prompt and appropriate measures when severe adverse events occur. In addition to the predicted adverse events, the possibility of emerging new symptoms cannot be ruled out and prompt action will be taken in such cases.

The recruitment of subjects started in November 2018 and will be completed by December 2020. The results will be announced within a few months of trial completion. Based on the study, if human safety, efficacy and the appropriate dose of SOCG are confirmed, this can be used as preliminary data supporting the utility of this Korean traditional medicine in treating depression, and to obtain a New Drug Application (NDA) for a phase III clinical trial. Further, we expect that this new antidepressant medication will be able to raise the depression cure rate among Koreans, alleviate the burden of medical expenses, and help revive the Korean medical herb industry.

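### The only comparison named for safety laboratory values is with baseline; no contrast with placebo or between doses is stated

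*Protocol article*

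**What the plan says.** All references are to the protocol article.

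- **Laboratory values (section 2.7.2):** "For safety assessment, outcomes of lab tests will be compared to the baseline values". The sentence names no test, no group contrast and no reference arm.
- **Adverse events (section 2.7.2):** these are handled by group. On presentation, the plan states: "Adverse events will be summarized based on groups and organs". On event counts, it states: "The ANOVA or Kruskal-Wallis test will be used to compare the frequency of medication-correlated adverse events between groups". On participants affected, it states: "The Pearson chi-squared test or Fisher's exact test will be used to compare the percentage of participants who experienced the adverse events at least once", and this too is a comparison across the arms.
- **Efficacy (section 2.7.2):** the primary outcome is analysed by ANCOVA with group, baseline score and institution, and reported as the difference between placebo and each SOCG group with a 95% confidence interval. Recovery and remission use placebo as the reference category.
- **General rule (section 2.7.2):** "We will compare data using analysis of variance (ANOVA) for the continuous variables, and Pearson chi-squared test or Fisher's exact test for the categorical variables". It is tied to no named variable or time point.
- **Design (section 2.1):** "Selected participants will be assigned to 3 experimental groups and 1 placebo group according to the stratified block randomization".
- **Prior human experience (section 3, Discussion):** "SOCG has not been tested on healthy individuals or patients, and therefore no side effects have been clearly revealed". The Introduction gives efficacy, safety and choice of dosage as the aims.

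**The concern.** Randomisation to placebo lets the trial attribute a change to the drug. A comparison with baseline within each arm does not use it. Anything that moves laboratory values over eight weeks regardless of treatment (seasonal or dietary change, assay drift, changes in health) will appear as a change from baseline in the active arms. For the few values with an eligibility limit, regression to the mean adds to this. A real effect running against such a drift can also be cancelled and missed.

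At stake is whether changes in, say, potassium or liver enzymes exceed those on placebo and differ between doses. With no earlier human data on SOCG to fall back on, this trial is where that question is first answered.

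**Working it through.** The plan gives no figure for this point, so there is none to reproduce. The check sets the two comparisons side by side under stated assumptions.

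**Inputs from the article**
- 37 participants per group (section 2.7.1), in four groups of which three are active (section 2.1).
- Significance level 5% (section 2.7.1), taken here as two-sided because the article does not say.

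**Assumptions (not in the article)**
- One laboratory variable, with normal change scores scaled to SD 1 and no missing values.
- No drug effect. The same shift *s* occurs in all four arms, with *s* = 0, 0.2, 0.3 or 0.5 SD.
- The comparison with baseline is a one-sample t-test of change within each arm, without multiplicity adjustment.

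**Before-after test in one arm.** The noncentrality is *s* × √37. For *s* = 0.3 this is 0.3 × 6.083 = 1.825, against a critical t of 2.028 on 36 degrees of freedom. The exact probability of significance is 0.427.

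**At least one of three active arms.** The arms are independent, so the probability is 1 − (1 − p)³. For *s* = 0.3: 1 − 0.573³ = 0.812.

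**Between-arm test.** One-way ANOVA of the change scores across the four arms. A common shift cancels, so the rate should stay near 5%.

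Results from 20,000 simulated trials, with the exact calculation in brackets:

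| Common shift (SD) | Before-after, a given active arm | Before-after, at least one of three | Between-arm ANOVA |
|---|---|---|---|
| 0 | 4.9% (5.0%) | 13.7% (14.3%) | 4.7% |
| 0.2 | 22.3% (22.0%) | 52.8% (52.5%) | 5.1% |
| 0.3 | 43.2% (42.7%) | 81.5% (81.2%) | 4.8% |
| 0.5 | 84.6% (84.1%) | 99.7% (99.6%) | 4.8% |

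The zero-shift row is multiplicity alone. The rise below it is the bias from a shared shift. A Bonferroni adjustment would lower these rates but not remove that bias.

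**Adverse event tests, checked for comparison.** With 37 per arm and mean counts of 0.1 to 1.0 per participant, Poisson or overdispersed, ANOVA on counts rejected a true null in 4.2% to 5.3% of trials and Kruskal-Wallis in 4.0% to 6.0%. Both are close to nominal.

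**The case against.** The strongest reply is that the laboratory sentence excludes nothing. The general rule compares continuous data by ANOVA and may have been meant to cover laboratory change. Section 2.5.3 has abnormal laboratory results entered in an adverse events report, so they can reach the between-group adverse event comparison. The article is a condensed account, and a fuller protocol or analysis plan may say more.

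Part of this stands. It is fair to say that baseline is the only comparison *named*, not that a placebo comparison is ruled out. But the general rule is tied to no variable and does not clearly override the specific sentence on laboratory safety. If it was meant to apply, the section gives two answers. The adverse event route misses changes that are not classed as abnormal. The point also concerns a comparator that the article states, not a detail it leaves out.

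A reader might infer more than the article supports:

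- **That drug-related harm cannot be isolated at all.** Adverse events are summarised by group, and the percentage of participants with at least one event is compared across placebo and the three doses by chi-squared or Fisher's exact test. That sentence states no relatedness limit of its own.
- **That ANOVA on event counts is invalid.** Kruskal-Wallis is offered as an alternative, and ANOVA held its size in the check above.
- **That a fixed number of false laboratory signals follows.** Section 2.1 lists 19 blood tests, and 19 × 4 arms × 0.05 = 3.8. But the article specifies no such set of 76 tests, the figure ignores the stated Bonferroni adjustment, and it measures multiplicity, not before-after bias. Placebo contrasts for three doses plus a trend test would also make 19 × 4 = 76 tests.
- **That regression to the mean affects every laboratory value.** Section 2.2.1 sets numerical limits only for ALT, AST, ALP and creatinine, and excludes hypokalemia. Most of the listed tests have no limit.

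**Conclusion.** The point holds for laboratory values. The sole comparison named for them is with baseline, and followed as written it does not separate drug effects from time effects. Under the stated assumptions, a common shift of 0.2, 0.3 or 0.5 SD gives a significant before-after change in at least one active arm in about 53%, 82% or 99.7% of trials with no drug effect, against about 5% for a between-arm test. The article gives no information on the size of any shift, so these figures show a range and do not predict this trial.

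For adverse events there is only a minor refinement. The frequency comparison is confined to events judged related to the medication, so it depends on investigators' attribution for a product whose side effects are not yet known. The absence of a dose-trend test is not an error. For assumed participant-level rates of 10%, 17%, 24% and 31%, the global chi-squared test has power of about 48% and a trend test about 66%, but that even rise is the pattern that favours the trend test.

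The laboratory analysis should be changed before unblinding. The efficacy analysis and the planned between-group adverse event comparisons are unaffected.

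**What to change.** Replace the laboratory sentence in section 2.7.2 with a between-group analysis:

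1. Analyse change in each continuous laboratory value by the ANCOVA already specified for other outcomes (group, baseline value, institution), and report each dose against placebo with a 95% confidence interval.
2. Add shift tables by group from baseline to the post-baseline assessment. Change from baseline within each arm can remain as description.
3. Report the between-group comparison of adverse event frequency for all events regardless of judged relatedness, alongside the related-only comparison.
4. Optionally, add a dose-trend analysis over 0, 1, 2 and 3 active tablets as a supplement.

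The cost is a few sentences of wording and some extra tables. No new data, visits or participants are needed.

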(1)Suicide risk.(2)Requirement of hospitalization.(3)Delusions, hallucinations, psychotic symptoms, or such a history.(4)Manic episodes, hypomanic episodes, mixed episodes or such a history.(5)Alcohol or other substance abuse/dependency issues or such a history.(6)Use of substances or drugs that may affect MDD symptoms (antianxiety drugs, antidepressants, antipsychotics, adrenocorticotrophic hormone drugs, estrogen preparations, L-dopa, digitalis, bromide, cyclosporine, disulfiram, isoniazid, yohimbine etc), unless 4 weeks have passed since the last use.(7)Hypokalemia or hypokalemia-inducible diseases (hypomagnesemia, Bartter syndrome, Gitelman syndrome, hyperaldosteronism inducible diseases, etc) or use of hypokalemia-inducible drugs (furosemide, thiazide, amphotericin, cisplatin, etc).(8)Use of warfarin.(9)Diagnosis of cardiac arrhythmia(10)Medical conditions that may affect the MDD symptoms (myocardial infarction, brain tumor, multiple sclerosis, pancreatic disease, hypo/hyperthyroidism, hyperparathyroidism, Addison's disease, Cushing's disease, Rheumatoid arthritis, cancer, cerebrovascular disease, dementia, epilepsy, etc).(11)Chronic diseases resistant to treatment (chronic active hepatitis, hypertension, diabetes mellitus, etc).(12)Treatment for hepatic tumor, hepatic cirrhosis, chronic renal failure, or congestive heart failure classified as New York Heart Association Class (NYHA Class) III–IV(13)Disabilities of hepatic or renal function (ALT, AST, ALP ≥ twice the upper limit of normal or creatinine > 2.0 mg/dL at screening).(14)Galactose intolerance, Lapp lactase deficiency, glucose-galactose malabsorption, or genetic problems.(15)Diseases that may influence drug absorption or digestive problems after associated surgery.(16)Participation in other clinical trials within the prior month.(17)History of hypersensitive or allergic reactions to drugs involved in the study.(18)Use of other herbal decoctions or extracts.(19)Difficulties in understanding the process of consent or in continuing to participate in the study due to mental retardation or cognitive problems.(20)Pregnancy or lactation.(21)Possibility of pregnancy and refusal to use contraceptive methods including double contraception^∗^, intrauterine contraceptive device, or spermicides during the study. ∗Double contraception is the use of barrier contraception (condom, diaphragm, etc) with other methods (sterilization surgery, intrauterine contraceptive device, contraceptive cream, jelly or foam).(22)Unsuitability for participation in the study due to other reasons.

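### The only comparison named specifically for laboratory safety data is with baseline; a comparison with the randomised placebo group is not clearly stated

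*Protocol article*

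**What the plan says.** In section 2.7.2 (Statistical analysis), the safety paragraph opens with the one sentence written specifically for laboratory data: "For safety assessment, outcomes of lab tests will be compared to the baseline values". It names no test, no significance level and no group contrast.

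Other statements bear on the point:

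- Also in 2.7.2, a general sentence reads: "We will compare data using analysis of variance (ANOVA) for the continuous variables, and Pearson chi-squared test or Fisher's exact test for the categorical variables". It does not say which data it covers. It is followed by "The size of the type I error caused due to multiple comparisons will be modified using Bonferroni's method", without a number of comparisons.
- The safety paragraph compares adverse events between groups. One test concerns the frequency of medication-related events. The other is to "compare the percentage of participants who experienced the adverse events at least once between the groups". Adverse events are also to be summarised by group and organ.
- Section 2.5.3 (Safety evaluation) links laboratory data to adverse events: "Every unintended phenomenon, side effects, abnormalities in vital signs, and lab tests will be documented in an adverse events report".
- For efficacy, 2.7.2 gives differences from placebo for the primary outcome and odds ratios with placebo as reference for recovery and remission. For the other secondary outcomes it specifies ANCOVA with a group term.
- The Discussion states: "SOCG has not been tested on healthy individuals or patients, and therefore no side effects have been clearly revealed".
- The exclusion criteria in 2.2.1 include "Hypokalemia or hypokalemia-inducible diseases", and section 2.1 lists potassium, liver enzymes, creatinine and CPK among the tests.

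**The concern.** A comparison with baseline does not use the randomisation. The mean change in an SOCG group is the drug effect plus whatever would have happened anyway over eight weeks: assay or handling changes, diet, regression to the mean. The placebo group estimates that second part, and subtracting it is the reason for having the group.

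Two errors can follow. Change shared by all groups can be read as an SOCG effect, or a real SOCG effect can be offset by shared change in the other direction and missed. The article intends this trial to establish human safety and an appropriate dose, and it is the first human exposure to the product. A dose-related shift in an analyte should therefore be read against placebo.

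**Working it through.** **1. What each statement delivers for a single analyte, such as potassium**

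| Statement | Uses the placebo group? | Isolates the analyte? |
|---|---|---|
| Laboratory sentence (2.7.2) | Not stated | Yes |
| General ANOVA / chi-squared sentence (2.7.2) | Yes, if it covers laboratory data; scope not stated | Yes, if it applies |
| Participants with at least one adverse event (2.7.2, with 2.5.3) | Yes | No: pooled with every other event |
| Frequency of medication-related adverse events (2.7.2) | Yes | No: pooled, and only events judged related |

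An abnormal value recorded as an adverse event therefore enters a between-group test, though not one specific to the analyte. A mean shift within the normal range enters one only if the general sentence is read to cover it.

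**2. Group size**

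Section 2.7.1 gives 37 per group with 5% dropout: 37 × 0.95 = 35.2, so about 35 evaluable, and 4 × 37 = 148 as stated. Both n = 35 and n = 37 are used below.

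**3. Assumptions not in the documents**

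SD of the eight-week potassium change 0.4 mmol/L; a drift common to all groups of 0.05 to 0.20 mmol/L; a true SOCG fall of 0.25 mmol/L; a two-sided 5% t-test within each group. The article does not name that test. It stands in for judging a group by its change from baseline.

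**4. Formulas**

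Power comes from the noncentral t distribution.

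- Before-after, one group: noncentrality = (net mean change / SD) × √n, df = n − 1.
- SOCG against placebo: noncentrality = (effect / SD) × √(n/2), df = 2n − 2. Common drift cancels.

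**5. No drug effect, common drift only**

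| Drift (mmol/L) | Noncentrality, n = 35 / 37 | Before-after significant, one SOCG group | One placebo contrast |
|---|---|---|---|
| 0.05 | 0.125√n = 0.74 / 0.76 | 11% / 11% | 5% |
| 0.10 | 0.25√n = 1.48 / 1.52 | 30% / 32% | 5% |
| 0.15 | 0.375√n = 2.22 / 2.28 | 58% / 60% | 5% |

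For at least one of three SOCG groups, 1 − (1 − p)³ gives about 30–31%, 66–68% and 92–94%. The matching figure for three unadjusted placebo contrasts is about 12% (simulation), not 5%.

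**6. True fall of 0.25 mmol/L**

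| Upward drift (mmol/L) | Net fall | Before-after detects, n = 35 / 37 | Placebo contrast detects, n = 35 / 37 |
|---|---|---|---|
| 0 | 0.25 | 95% / 96% | 73% / 76% |
| 0.15 | 0.10 | 30% / 32% | 73% / 76% |
| 0.20 | 0.05 | 11% / 11% | 73% / 76% |

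For the placebo contrast the noncentrality is 0.625 × √(n/2) = 2.61 / 2.69. With Bonferroni for three contrasts (α = 0.05/3) its power falls to about 57% / 60%.

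**7. Reading**

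With no drift the before-after test is the more sensitive, because it carries the sampling error of one group instead of two. Its weakness is bias: nothing in the data of a single group shows whether drift is zero.

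**The case against.** A reader might infer that the plan excludes placebo from the laboratory analysis. The documents do not support that. The sentence names baseline as comparator and is silent on groups; it is compatible with change scores or shift tables shown by group. The general ANOVA sentence could cover laboratory changes. Section 2.5.3 sends laboratory abnormalities into the adverse event comparisons, and events are summarised by group and organ, so a large shift would be seen against placebo in some form.

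It can also be said that this is a journal article, and that table layouts and models for each analyte commonly sit in the full protocol or SAP. That excuses missing detail. It does not settle a comparator that the article itself states, in a paragraph that specifies between-group tests for adverse events.

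The illustration is open to challenge too. The SD, drift and effect are assumed, and no per-group test is named. The loss of detection in step 6 needs an opposing drift of 60–80% of the effect (0.15/0.25 and 0.20/0.25). Recruitment over about two years would partly average out season and assay changes, and the four-week washout and the drug exclusions limit carry-over from earlier treatment. These points stand as limits on size. They make large drift less likely, but they do not make a before-after comparison able to recognise it.

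**Conclusion.** The point holds in a limited form. The only laboratory-specific comparison stated is with baseline, and analyte-level mean shifts within the normal range have no clearly stated comparison with placebo. It would be too strong to say that laboratory data are never compared with placebo.

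The size depends on the drift, which the documents do not give. Under the assumptions in step 3, the false-signal rate per SOCG group runs from about 11% at 0.05 mmol/L to 58–60% at 0.15 mmol/L, against 5% for one placebo contrast. Detection of a true fall of 0.25 mmol/L by the before-after test runs from 95–96% with no drift to about 11% with an opposing drift of 0.20 mmol/L, against 73–76% for the placebo contrast throughout. The argument that baseline alone cannot separate drug effect from shared change needs none of these figures.

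The change should be made: it is cheap, and this is the product's first human safety dataset.

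**What to change.** Replace the laboratory sentence in 2.7.2 with wording such as:

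*For each laboratory analyte, change from baseline will be compared between each SOCG group and placebo by ANCOVA with group, baseline value and institution as explanatory variables, and differences will be given with 95% confidence intervals. Shifts from normal to abnormal, by the laboratory reference range, will be tabulated by group including placebo. Within-group change will be descriptive only.*

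Also state whether the Bonferroni rule applies to these safety estimates. The present wording does not say, and applying it to three contrasts would lower power in the illustration from 73–76% to about 57–60%. The shift tables should use the reference range, because the liver enzyme and creatinine cut-offs in 2.2.1 are screening exclusions and are not stated as on-treatment limits.

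The cost is a few extra tables. No new data, visits or participants are needed, and the model is the one already planned for efficacy. The downside is several safety comparisons for which the trial is not powered; they should be read as estimates with intervals, and a non-significant difference should not be taken as evidence of safety.

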**Discussion and Conclusions::**

Demonstration of human safety and efficacy of SOCG in the present trial and identification of the appropriate dose will justify a New Drug Application and a phase III clinical trial. Further, we expect that this new antidepressant will be able to increase cure rates, and alleviate the burden of medical expenses.

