#### Sample size

2.7.1

The sample size required is based on results of the t-test for independent samples comparing changes in the K-HRDS score from baseline to the last observed one during the 8 weeks of treatment between the SOCG medium dose group and the placebo group.

Because no relevant results of clinical trials have been reported, the sample size was calculated referring to a clinical trial of similar design involving patients with depression.^[15]^

The sample size of each group is 37, considering a significance level of 5%, a power of 80%, and assigning a ratio of 1:1:1:1 and a dropout rate of 5%.

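### Section 2.7.2 compares adverse events between arms by significance tests without risk differences or intervals; at 37 per arm these tests cannot support the article's wording that human safety is demonstrated or confirmed

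*Protocol article*

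**What the plan says.** **Safety analysis (section 2.7.2).** Laboratory results are compared with baseline. Each adverse event is listed and explained, frequencies are recorded by relation to the medication, and events are summarized by arm and organ. Two comparisons between groups carry a test. The frequency of medication-related events is compared by ANOVA or Kruskal-Wallis. For incidence, meaning one event or more per participant, the plan reads: "The Pearson chi-squared test or Fisher's exact test will be used to compare the percentage of participants who experienced the adverse events". No risk difference, interval or margin is named.

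**Efficacy analysis (same section).** For the primary outcome the plan asks for more than a test, in a list that closes with the P-value: "The estimates of mean differences between placebo and each SOCG group, the 95% confidence interval, and the". For recovery and remission it asks for an odds ratio for each SOCG group against placebo with a 95% interval.

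**What is claimed.** The Abstract, which in the same sentence looks ahead to phase III, states: "Demonstration of human safety and efficacy of SOCG in the present trial and identification of the appropriate dose will justify a New Drug Application". The Discussion is conditional: "if human safety, efficacy and the appropriate dose of SOCG are confirmed", the results can serve as preliminary data. The Discussion also records that "SOCG has not been tested on healthy individuals or patients, and therefore no side effects have been clearly revealed".

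**Sample size (section 2.7.1).** There are 37 per group, set for the K-HDRS change in the medium dose group against placebo.

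**The concern.** The method named for the safety comparison and the safety wording do not fit together. A test of no difference can give evidence of a difference. It cannot give evidence that there is none, and its P-value does not say how large an excess of harm remains compatible with the data. In a small trial a non-significant result is likely even when harm is real.

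The trial is meant to inform the choice of a dose to take forward, and there are no earlier human data to lean on. A report that says adverse events did not differ significantly would tell a reader little. A report that gives the risk difference and its interval would say how much excess risk has been excluded. The plan already takes that approach for the primary outcome and for recovery and remission.

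**Working it through.** **Inputs from the article.** 37 per arm, four arms, allocation 1:1:1:1, 5% dropout, significance level 5% (section 2.7.1). All participants who took the medication at least once are assessed for adverse events (section 2.5.3), so up to 37 per arm.

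**Assumptions.** The article gives no adverse event rate. I take a rise from 10% to 20% as the main case and vary it. Tests are two-sided at 5%; the article does not state the sidedness.

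**The plan's own figure.** The effect size and SD behind the sample size are not in the article, so 37 cannot be rebuilt from its inputs. The dropout step is consistent: 35 / (1 - 0.05) = 36.8, rounded up to 37, and 4 x 37 = 148. There is no stated power for safety to reproduce.

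**Two-arm miss rate.** Miss rate = 1 - sum over all pairs (a, b) of P(a events on placebo) x P(b events on one dose), for those pairs where the test gives P at or below 0.05. Both counts are binomial with n = 37. Results by exact enumeration:

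| Placebo v dose (assumed) | Pearson, uncorrected | Fisher |
|---|---|---|
| 5% v 10% | 86.5% | 96.5% |
| 10% v 20% | 77.0% | 85.8% |
| 20% v 40% | 52.5% | 61.8% |
| 30% v 60% | 25.8% | 34.0% |

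The miss rate for a doubling therefore runs from about 26% to 97%, and is worst for uncommon events.

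**Four-group miss rate.** The article words the test as a comparison between the groups, so the Pearson test on 3 degrees of freedom is also relevant. By simulation (400,000 trials per pattern), with placebo at 10%:

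| Pattern over the three doses | Missed |
|---|---|
| one dose at 20%, others at 10% | 77% |
| linear rise to 20% | 85% |
| all three at 20% | 83% |
| two at 20%, one at 10% | 74% |

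The conclusion does not depend on using the two-arm test.

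**What an interval would show.** Suppose 4/37 (10.8%) on placebo and 9/37 (24.3%) on one dose have an adverse event. Fisher's test gives P = 0.22. The risk difference is 13.5 percentage points, with a Newcombe 95% interval from -4 to +31. The test alone reads as no significant difference; the interval shows that an excess of up to 31 points is not excluded.

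**Expected precision.** At 10% v 20%, the half-width is 1.96 x sqrt(0.10 x 0.90/37 + 0.20 x 0.80/37) = 0.161, about 16 points for one dose against placebo. For the three doses pooled (3 x 37 = 111), it is 1.96 x sqrt(0.10 x 0.90/37 + 0.20 x 0.80/111) = 0.122, about 12 points.

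**The case against.** A reader might infer that the plan will treat a non-significant test as proof of safety, or that such a result is its only way to a safety conclusion between arms. The article supports neither. It states no such rule. A safety judgement can also draw on the event listings, the assessed relation to the medication, seriousness, the laboratory results and the summaries by arm and organ. The tests are the only inferential between-arm comparison named, not the only safety output.

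A reader might also infer that the trial is too small. Low power for adverse events is usual in a phase II trial sized for efficacy, and the article openly ties its sample size to K-HDRS. About 199 per arm would be needed for 80% power at 10% v 20%; that shows the scale and is not a request. Reporting intervals would not raise the power.

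The safety wording is also less firm than the Abstract alone suggests. The Introduction aims to assess safety, and the Discussion is conditional, speaks of preliminary data, and says that side effects remain possible.

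Finally, this is a condensed article, and a full protocol or SAP may already plan intervals. That is a fair reason to call the point minor. It does not remove it: the article names its safety tests, asks for estimates with intervals for efficacy outcomes in the same section, and in the Abstract claims more for safety than those tests can show.

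**Conclusion.** The point holds as a minor, cheap improvement. The inferential between-arm safety comparisons named are tests of no difference, without the estimates and intervals required for the primary outcome and for recovery and remission. At 37 per arm they cannot support wording that safety is demonstrated or confirmed.

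The size rests on assumed event rates and a two-sided 5% level. The main case of 10% against 20% is more likely to be missed than found under either two-arm test and under every four-group pattern tried. At a high base rate the position is better: a rise from 30% to 60% would usually be detected. The finding concerns what the tests can show and how the safety claim is worded. It is not a finding that the sample size is wrong or that the sponsor has adopted a faulty safety rule.

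**What to change.** - In section 2.7.2, alongside or in place of the adverse event tests, report the risk difference in participants with at least one adverse event, with an unadjusted 95% interval (for example Newcombe). Do this for each SOCG dose against placebo and for pooled SOCG against placebo.
- State there that a non-significant comparison is not evidence of safety.
- In the Abstract and the Discussion, replace the wording that safety is demonstrated or confirmed with initial human safety data, together with the excess risk against placebo that the trial can exclude.

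The cost is a few extra columns in the safety tables and a more modest safety claim. No extra participants, visits or procedures are needed. If the full protocol or SAP already plans these intervals, only the wording of the article needs to change.
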